#### Secondary objectives

The secondary objectives are to determine whether an adjunctive slow-release dexamethasone implant, given at the time of surgery, has an effect on the following at 6 and 12 months following the primary study vitrectomy:

•visual acuity (Early Treatment Diabetic Retinopathy Study (ETDRS) method)

•macula oedema and thickness (spectralis domain optical coherence tomography (SD-OCT) analysis)

•development of overt PVR recurrence at any time point

•complete retinal reattachment

•posterior (post equatorial) retinal reattachment

•tractional retinal detachment

•hypotony or raised intraocular pressure (IOP)

•macula pucker or epiretinal membrane (ERM)

•cataract

•quality of life as assessed by NEI VFQ25, SF36 and depression screening questionnaires
[29]

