### Eligibility

#### Inclusion criteria

1. All patients with established PVR (Grade C) following rhegmatogenous retinal detachment requiring surgery with planned silicone oil tamponade

2. Ability to give informed consent

3. Willingness to accept randomisation and attend follow-ups

Where the disease is bilateral at the time of screening, the worst affected eye (in terms of severity of PVR) will be included in the study.

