### Screening and baseline assessment

An initial screening assessment will be performed prior to recruitment to confirm that patients satisfy all inclusion and exclusion criteria. This will include a full ophthalmic examination with slit-lamp/indirect biomicroscopy and consider the patient’s medical history and concomitant medication.

Clinical findings documented as part of the routine clinical care at the time of screening may be used to populate data in the baseline CRF and used as part of the study data (if collected within 1 week of the study vitrectomy). This information may be collected prior to informed consent for enrolment into the trial as no additional intervention is performed outside routine clinical care.

Baseline assessments will be performed within 1 week of the scheduled operation date. This will include: patient demographics, past ocular history, logMAR visual acuity (ETDRS method), slit lamp/indirect ophthalmic examination (anterior and posterior segment assessment, lens status, extent of retinal detachment, grade of PVR
[32]), SD-OCT-guided foveal thickness and volume, and quality of life questionnaires.

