#### Secondary

Secondary outcomes will be performed at 6 and 12 months following the primary study vitrectomy:

•visual acuity: a comparison of the median visual acuity and the proportion of patients in each group achieving a visual acuity of 55 ETDRS letters or better

•macula oedema and thickness (SD-OCT analysis), that is the proportion of patients in each group with a central A1 macula subfield measure of >300 μm

•the proportion of patients in each group who develop overt PVR recurrence

•the proportion of patients in each group achieving complete retinal reattachment

•the proportion of patients in each group achieving stable posterior (post equatorial) retinal reattachment

•the proportion of patients in each group with a tractional retinal detachment

•the proportion of patients in each group who suffer hypotony (defined as IOP <6 mmHg and/or raised IOP (defined as >25 mmHg) at any time during the study period

•the proportion of patients in each group who develop macula pucker or epiretinal membrane (ERM) and/or require macula ERM surgery at any time during the study

•the proportion of patients in each group who require cataract surgery at any time during the study

•quality of life assessment: a comparison of the median or mean scores of both SF36 and VFQ25 between both groups and the proportion of patients with severe depression
[29]

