### Trial size and timescale

Based on the results of the primary outcome measure from a trial of the same patient group carried out in the study centres
[7], 66 patients per study arm are required for a study power of 85% to detect, at the 5% level, a 50% improvement in the success of the adjunctive regime (reducing failure from 49% to 24%). A 50% reduction in failure would represent a marked clinical benefit and would be likely to be adopted on a large scale by vitreoretinal surgeons. Our pilot study has shown that this is a realistic treatment difference. Given a 5% loss to follow-up and protocol violations (previous similar studies at Moorfields had rates of 3% to 5% loss to follow-up or protocol violation
[7-9]), this gives a study total of 140 patients to be randomised.

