### Secondary endpoint analysis

Summary statistics will be computed for changes in visual acuity for the two treatment groups at 6 and 12 months and the proportion of patients in each group who suffer any adverse events will be summarised. The exact binomial method will be used to compute 95% confidence intervals. Summary statistics for all other secondary outcomes will be provided by treatment group and if statistical comparisons are made, results will be reported as exploratory.

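### Quality of life is compared without a stated use of the baseline questionnaires, and depression only as severe or not: unbiased, but less precise than the data allow

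*Protocol article*

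**What the plan says.** Under Secondary objectives the protocol lists "quality of life as assessed by NEI VFQ25, SF36 and depression screening questionnaires". The Secondary part of Outcome measures turns this into an outcome: "a comparison of the median or mean scores of both SF36 and VFQ25 between both groups and the proportion of patients with severe depression". The timing is given by "Secondary outcomes will be performed at 6 and 12 months following the primary study vitrectomy".

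The baseline visit, within a week of surgery, includes "SD-OCT-guided foveal thickness and volume, and quality of life questionnaires". No section says how the baseline questionnaires enter the quality-of-life comparison. Secondary endpoint analysis refers to change for one outcome only: "Summary statistics will be computed for changes in visual acuity for the two treatment groups at 6 and 12 months". For the rest it says "Summary statistics for all other secondary outcomes will be provided by treatment group and if statistical comparisons are made, results will be reported as exploratory".

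One eye per patient is studied. When both eyes are affected, "the worst affected eye (in terms of severity of PVR) will be included in the study".

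**The concern.** The questionnaires score the patient, while the implant goes into one eye. Patients will differ in fellow-eye vision, general health and mood before surgery. In a comparison of follow-up scores alone, all of that variation stays in the error term. The baseline score carries part of it and has already been collected.

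The depression questionnaire loses information in a second way. Reduced to one severe category, it cannot register any change in mood that does not cross that cut-off.

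At stake is how informative a named secondary objective can be. Wide intervals that include zero could be taken to mean that the implant makes no difference to patients, when the analysis had limited ability to show one. The primary outcome and the sample size are not affected.

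**Working it through.** **Inputs from the protocol.** 66 per arm, 85% power, 5% level, failure 49% against 24%, 5% loss, 140 in total (Trial size and timescale).

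**Inputs assumed, because the protocol gives none.** Baseline to follow-up correlation r = 0.5 to 0.7; quality-of-life effects of 0.3 and 0.5 SD; control-arm rate of severe depression 2% to 20%, halved by treatment.

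**Step 1: the plan's own figure.** The protocol states "66 patients per study arm are required for a study power of 85% to detect, at the 5% level". The two-sided pooled-variance formula for two proportions, without continuity correction, gives 66 per arm for 49% against 24% (power 85.5%). Allowing for 5% loss, 132 / 0.95 = 138.9, so 139, which agrees with 140. The sample size reproduces and is not in dispute. The steps below use 66 per arm.

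**Step 2: variance.** Adjusting for the baseline score multiplies the residual variance by 1 − r² and the interval width by √(1 − r²).
- r = 0.5: 1 − 0.25 = 0.75, so 25% of the variance is removed; √0.75 = 0.87, so intervals are 13% narrower.
- r = 0.7: 1 − 0.49 = 0.51, so 49% is removed; √0.51 = 0.71, so intervals are 29% narrower.

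**Step 3: power for a mean score.** Two-sided 5% t-test, noncentrality d·√(66/2) / √(1 − r²).

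| Analysis | Power at 0.3 SD | Power at 0.5 SD | Difference detectable with 80% power |
|---|---|---|---|
| Follow-up score alone | 40% | 81% | 0.49 SD |
| Adjusted, r = 0.5 | 51% | 91% | 0.42 SD |
| Adjusted, r = 0.6 | 57% | 95% | 0.39 SD |
| Adjusted, r = 0.7 | 67% | 98% | 0.35 SD |

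The last column is (1.96 + 0.84)·√(2/66)·√(1 − r²).

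**Step 4: severe depression.** Expected control cases are 66 × rate. Power is the exact power of Fisher's test, two-sided 5%, for a halving.

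| Assumed control rate | Expected control cases | Power for a halving |
|---|---|---|
| 2% | 1.3 | 0.1% |
| 5% | 3.3 | 2.7% |
| 8% | 5.3 | 7.2% |
| 10% | 6.6 | 10% |
| 20% | 13.2 | 28% |

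With no cases in one arm, 5 against 0 gives p = 0.058 and 6 against 0 gives p = 0.028.

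**Step 5: what adjustment cannot do.** Suppose that only half the patients' scores respond to the study eye, so that a 0.5 SD effect averages 0.25 SD. Power is then about 30% without adjustment and about 43% with adjustment at r = 0.6. Adjustment narrows the interval but does not restore the diluted effect.

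**The case against.** **The analysis plan may settle this.** The protocol says that a statistical analysis plan will be written before the analysis. Covariate adjustment of a secondary score is usual content for it, and the outcome wording does not exclude adjustment. This stands in part: a reader might infer that the protocol commits to unadjusted scores, and it does not say that. It does, however, fix a comparison of medians or means and a severe-depression proportion as the outcome, and an analysis plan that follows it literally would inherit both.

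**The comparison is valid as it is.** This stands. Randomisation keeps the unadjusted comparison unbiased, and its confidence interval already allows for chance imbalance at baseline.

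**A patient-level score is a proper outcome.** This stands too. Whether treating one eye helps the patient is a fair question, so the choice of questionnaires is not a flaw. The worse-eye rule covers bilateral disease only, and the protocol does not say how common that is.

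**Stronger readings fail.** A reader might infer that the severe category will be almost empty. The protocol gives neither a rate nor a cut-off, and at 20% there would be about 13 control cases. A reader might also infer that any benefit would be hidden whatever the implant does. Step 3 contradicts that: an average effect of 0.5 SD has about 81% power unadjusted.

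**The results are exploratory.** True, and this limits the weight of the point. It does not make the less precise analysis preferable when the better one uses data already in hand.

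**Conclusion.** The point holds as a minor, free improvement. The protocol collects baseline questionnaires, states no use for them in the quality-of-life comparison, and reduces depression to a single category.

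The loss is one of precision. Its size depends on a correlation that the protocol does not give, and at a modest effect it is worth having. The weakness of the severe-depression proportion does not hinge on the category being rare, since power for a halving stays low across the whole assumed range.

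No bias is shown and the primary conclusion is untouched. The protocol does not support a claim that a real effect would be missed regardless of its size. Dilution by the fellow eye would remain after the change.

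**What to change.** In the analysis plan:
- Report VFQ25 and the SF36 summary scores at 6 and 12 months as mean differences between arms with 95% confidence intervals, from a regression adjusted for the same score at baseline.
- Analyse the depression questionnaire as its full score, adjusted for its baseline value.
- Keep the proportion with severe depression as a descriptive line.
- Keep all of these results labelled exploratory, and state that adjustment improves precision without removing dilution by the fellow eye.

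The cost is wording only. The data are already collected, and no extra patients, visits or questionnaires are needed.

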### Adverse events and safety reporting

Safety reporting will adhere to the sponsor’s standard operating procedures and the trial team are confident that means are in place to monitor, record and report adverse events in line with guidelines issued by the Medicines and Healthcare Products Regulatory Agency (MHRA). There is an external data monitoring committee, who have an agreed charter. They will meet six to twelve monthly or on an *ad hoc* basis as required.

Expected adverse events are as follows:

1. Cataract

2. Raised IOP

3. Hypotony

4. Sterile hypopyon

5. Retinal detachment

6. Uveitis

7. Further surgery

8. Glaucoma

9. Headache

10. Migraine

11. Vitreous opacities

More specifically, the recording of the severity of raised IOP will be as follows:

Mild: >25 mmHg and <35 mmHg

Moderate: ≥35 mmHg

Severe: Any interventional invasive procedure (for example, surgery or laser treatment) required to control the elevated IOP acutely or long-term, during the study period

Unexpected adverse events will include:

1. Endophthalmitis

2. Systemic illness

3. Ocular vascular occlusion

4. Other

### Trial size and timescale

Based on the results of the primary outcome measure from a trial of the same patient group carried out in the study centres
[7], 66 patients per study arm are required for a study power of 85% to detect, at the 5% level, a 50% improvement in the success of the adjunctive regime (reducing failure from 49% to 24%). A 50% reduction in failure would represent a marked clinical benefit and would be likely to be adopted on a large scale by vitreoretinal surgeons. Our pilot study has shown that this is a realistic treatment difference. Given a 5% loss to follow-up and protocol violations (previous similar studies at Moorfields had rates of 3% to 5% loss to follow-up or protocol violation
[7-9]), this gives a study total of 140 patients to be randomised.

### Proposed timescale

Trial start: February 2012

Projected trial end: February 2015

Trial duration: 36 months

Duration of each patient’s participation: 12 months

### Statistical analyses

The statistical analysis plan will be written in advance of the data analysis by the trial statistician and will be approved by the trial steering committee. Analysis will be by intention to treat (ITT) to retain validity of the randomisation process. The trial ITT population comprises all randomised patients regardless of eligibility (inclusion/exclusion) errors, post randomisation withdrawal and whether the correct study treatments were received. Data analysis will adhere to the CONSORT guidelines for randomised controlled trials. The baseline characteristics of the two groups will be compared to assess the adequacy of randomisation.

### Primary endpoint analysis

The chi-square test will be used to assess the statistical significance of any observed differences between the proportions of patients who 'fail’ as defined by the primary outcome measures at 6 months in the two groups. Logistic regression will be conducted to assess for any baseline covariates believed to be associated with the outcome.

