## Discussion

This randomised controlled trial investigating the use of a sustained-release dexamethasone implant will be the first to evaluate its role as an adjunctive agent, in patients undergoing vitreoretinal surgery for retinal detachment with established PVR.

Our projected recruitment rate is based on a retrospective audit of the incidence of relevant cases at the study site. Due to the poor prognosis associated with current standard treatment, we expect a high recruitment uptake following successful eligibility screening. We remain optimistic that our recruitment target will be met within the projected timescale.

We accept that although our inclusion criteria specifies Grade C PVR requiring surgery with silicone oil, the cohort of participants is likely to be quite a heterogeneous group. The severity of Grade C PVR can vary widely throughout its sub-classification both in terms of extent (number of clock hours) and distribution (focal, diffuse, anterior, posterior or subretinal). However, we expect the adequacy of randomisation to compensate for this and shall acknowledge any unequal weighting within the groups as limitations of the study. We do, however, accept that we may limit our sensitivity to small differences between the two groups.

As this single centre study serves a wide geographical catchment area with a broad patient demographic representative of the UK, we do not expect the results to provide a misleading estimate of treatment effect. Again, we expect the adequacy of randomisation to compensate for any variation of effect between ethnicities.

The authors acknowledge the limitations of a single masked study, but have made every effort to reduce investigator bias. As the IMP is no longer visible inside the eye after approximately 8 weeks, it is unlikely that the investigators will be aware of the treatment allocation of the participant at the time of the primary and secondary outcome assessments. The trial team considered using an independent assessor of the primary outcome measure at 6 and 12 months, but felt that there was insufficient evidence to suggest this was necessary and that it added additional unjustifiable cost to the study.

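### The primary chi-square is valid but ignores recorded PVR severity; prespecified adjustment would gain about 0 to 6 points of power and account for chance imbalance

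*Protocol article*

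**What the plan says.** All places are in the protocol article.

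- **Primary endpoint analysis.** The test is fixed: "The chi-square test will be used to assess the statistical significance of any observed differences between the proportions of patients who" fail at 6 months. A second sentence adds: "Logistic regression will be conducted to assess for any baseline covariates believed to be associated with the outcome". It names no covariate and mentions no adjusted treatment effect.
- **Recruitment and randomisation.** Allocation uses permuted blocks of differing size, from one list of 140 study IDs issued in order. No stratification factor is stated.
- **Screening and baseline assessment.** The baseline examination includes "extent of retinal detachment, grade of PVR".
- **Statistical analyses.** "The baseline characteristics of the two groups will be compared to assess the adequacy of randomisation". The SAP is still to be written, before the data are analysed.
- **Discussion.** Grade C severity is said to differ widely in clock hours and distribution. The response is: "we expect the adequacy of randomisation to compensate for this and shall acknowledge any unequal weighting within the groups as limitations of the study". Reduced sensitivity to small differences is accepted.
- **Trial size and timescale.** "66 patients per study arm are required for a study power of 85% to detect, at the 5% level, a 50% improvement", with failure falling from 49% to 24%.

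**The concern.** The protocol identifies a likely prognostic factor, records it before surgery, and then leaves it out of both the allocation and the primary test. Randomisation removes bias on average. It does not guarantee balance in one trial of 140 patients, and it does not recover the precision that a recorded prognostic variable offers. Blocking from a single list balances numbers between arms, not severity.

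Two things are at stake. One is some power that could be had from data already collected. The other is how a chance imbalance would be handled. If the arms differ in severity, the chi-square takes no account of it, and an adjusted result first specified after the imbalance has been seen would be post hoc.

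**Working it through.** **1. The plan's own figure.** Inputs from Trial size and timescale: p1 = 0.49, p2 = 0.24, 5% level (two-sided assumed), 85% power. Mean proportion 0.365.

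n per arm = [1.960 × √(2 × 0.365 × 0.635) + 1.036 × √(0.49 × 0.51 + 0.24 × 0.76)]² / 0.25²

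= [1.334 + 0.681]² / 0.0625 = 65.02, rounded up to 66.

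Power at 66 per arm is 85.5%. With "Given a 5% loss to follow-up and protocol violations", 66 / 0.95 = 69.5, so 70 per arm and 140 in total. The stated size reproduces for a two-sided chi-square without continuity correction.

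**2. Power with and without adjustment.** The documents do not say how strongly severity predicts failure, so the odds ratio per SD was varied from 1 to 3. Each setting used 4,000 simulated trials with 66 per arm, one normally distributed severity score, and marginal failure held at 49% and 24%. The unadjusted chi-square was compared with the likelihood-ratio test for arm in a logistic model containing the score. The Monte Carlo standard error of each power is about 0.5 points. Type I error was simulated with 49% failure in both arms.

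| Assumed OR per SD | Power, chi-square | Power, adjusted | Gain (points) | Type I, chi-square | Type I, adjusted |
|---|---|---|---|---|---|
| 1.0 | 86.6% | 86.5% | about 0 | 4.8% | 5.1% |
| 1.5 | 85.8% | 86.9% | about 1 | 4.4% | 5.3% |
| 2.0 | 87.1% | 89.5% | 2 to 3 | 5.1% | 5.5% |
| 3.0 | 86.1% | 92.1% | 6 | 4.3% | 5.1% |

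**3. Chance imbalance.** For a feature with prevalence q and 66 per arm, the between-arm difference has SD = √(q(1 − q) × 2/66).

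- q = 0.3: SD 8.0 points. Chance of a gap of at least 10 points 21%, of at least 15 points 6%.
- q = 0.5: SD 8.7 points. Chance 25% and 8.5%.

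**4. What such a gap would do.** The shift in the crude difference is the imbalance times the difference in failure risk between patients with and without the feature. On assumed risk differences of 20 and 30 points, a 10-point gap shifts the arm comparison by 0.10 × 20 = 2 or 0.10 × 30 = 3 points. The design difference is 49 − 24 = 25 points. The shift can go in either direction.

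**5. Room for covariates.** Expected failures at 66 per arm are 66 × 0.49 + 66 × 0.24 = 32.3 + 15.8, about 48. Arm, severity and one or two further single-term factors make 3 or 4 terms, that is 48/3 = 16 or 48/4 = 12 failures per term.

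**The case against.** The strongest reply is that nothing in the primary analysis is wrong. A chi-square is valid for two randomised proportions, its type I error already covers chance imbalance over repeated trials, and the trial was sized for exactly this test. That stands. Several stronger readings are tempting, and the documents do not support them.

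- **That the trial is underpowered.** It has the power it states. The Discussion concedes sensitivity only to small differences, whereas the design targets 25 points.
- **That imbalance would be uncorrectable.** The baseline data needed to adjust are to be collected.
- **That the logistic regression is an outcome-driven search.** Its wording can equally mean covariates chosen on prior belief. The SAP may name them and report an adjusted effect. What the article does settle is that the chi-square is the primary test.
- **That the baseline comparison means significance testing.** No such tests are mentioned, and the same section commits to CONSORT.
- **That clock hours are a recorded baseline field.** The baseline list gives grade of PVR and extent of detachment. Clock hours appear only in the Discussion, as part of the Grade C sub-classification, so their recording is likely but not stated.

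The size of the gain is also open to challenge. All patients are Grade C, which narrows the range of severity. The simulation assumes one correctly modelled score measured without error. The adjusted test's simulated type I error was slightly higher (5.1% to 5.5% against 4.3% to 5.1%), so part of a small gain may reflect that.

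What survives is that the response to a foreseen imbalance is a stated policy of acknowledging it. That is more than detail left to the SAP.

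**Conclusion.** The point holds as an efficiency and robustness improvement. The primary test is valid and the sample size is correct for it. Prespecified adjustment would add between nothing and about 6 points of power. Where it falls in that range depends on an association that the documents do not quantify; the upper end needs an odds ratio near 3 per SD and a well-measured severity score. The second benefit is that an imbalance of 10 points or more, which has about a 21% to 25% chance for a feature held by 30% to 50% of patients, would be handled by a rule fixed in advance. On the assumed risk differences, such an imbalance would move the result by 2 to 3 points, modest beside the 25-point target.

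**What to change.** Before analysis, specify as primary a logistic regression of 6-month failure on arm plus baseline PVR severity (grade or extent, as recorded) and at most one or two other named baseline factors, such as extent of detachment. State how each factor is coded. Report a standardised risk difference with 95% CI alongside the odds ratio; this keeps the result on the scale used for the sample size, since an adjusted odds ratio is not directly comparable with the crude one. Keep the chi-square as the unadjusted supporting analysis. State separately whether the regression assessing other covariates is exploratory.

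The cost is analysis-plan wording and slight extra analysis work. No new patients, visits or measurements are needed, and the sample size can stay. If severity turns out not to be prognostic, nothing is gained.
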